#### Sensitivity analysis of the primary endpoint measure

The primary endpoint analysis will be repeated in the per-protocol and surgical site infection population. Further sensitivity analyses will be performed as follows: (a) in the surgical site infection population, all missing data will be imputed as surgical site infections in both groups; (b) in the surgical site infection population, all missing data will be imputed as non-surgical site infection in both groups; (c) in the surgical site infection population, missing data will be imputed as surgical site infections in the intervention group, but as non-surgical site infection in the control group; (d) a time-to-event analysis will be performed in the surgical site infection population according to Kaplan–Meier analysis.

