### Sample size

A total of 152 patients will be analyzed per group. Given an estimated drop-out rate of approximately 10 %, 340 patients will be randomized to the two treatment arms.

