### Statistical methods

#### Sample size calculation

Sample size calculation is based on the primary endpoint measure (whether or not there is surgical site infection, according to CDC) within 30 days post operation [9] and was conducted by using nQuery Advisor® software version 7.0 (Statistical Solutions Ltd, Cork, Ireland). Based on the assumption that the percentage of patients developing postoperative wound infections in a surgical population undergoing open colorectal surgery is approximately 25 % for the control group (based on results from previous randomized controlled trials in abdominal surgery [14, 15, 17]) and can be reduced to 12.5 % in the experimental intervention arm, a group sample size of 152 patients would need to be compared using the chi-square test, to achieve 80 % power in detecting this difference in surgical site infection rate at a two-sided level of significance of 5 %. Under the assumption of a drop-out rate of up to 15 %, a total of 340 patients (170 per group) need to be enrolled in the study. Owing to the broad inclusion criteria and the limited number of exclusion criteria, the limited study time per patient (30 days), as well as the comprehensible nature of the trial, no more than 100 patients are expected to fail the screening process. Therefore, the total number of patients needed for screening is 440 (Fig. 1).

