##### Surgical site infection population

The surgical site infection population contains all patients included in the intention-to-treat population who have reached the study end (visit 6), independent of the treatment they have received (‘as randomized’).

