#### Prespecified subgroup analysis

Prespecified subgroup analysis will be performed in the surgical site infection population for the depth of surgical site infection (superficial versus deep versus organ space; Table 1) in both groups (NPIT versus control). Furthermore, the rate of all surgical site infections will be analyzed in the surgical site infection population in the following subgroups: (a) National Nosocomial Infection Surveillance risk score (0 versus 1 versus >1); (b) body mass index (<25 versus >25); (c) grade of contamination (clean versus clean-contaminated versus contaminated versus dirty, as defined by the CDC, [9]); (d) American Society of Anesthesiology score (1 and 2 versus 3 versus ≥4); (e) presence of an ostomy (yes versus no); (f) skin preparation used (ethanol-based versus isopropyl-alcohol-based versus chlorhexidine-based versus Povidone-iodine-based); (g) age (≤65 versus > 65 years), (g) cause of surgery (malignant versus benign surgery).

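### Missing-data sensitivity analyses (a)–(c) are set in a population of patients who completed follow-up, where almost nothing is missing, so they barely test the primary imputation rule

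*Protocol article*

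**What the plan says.** The primary analysis is in the ITT population (Analysis of the primary endpoint measure). Under Intention-to-treat population, an outcome missing through death or relaparotomy counts as an SSI in both arms, and an outcome missing for any other reason, such as loss to follow-up, counts as no SSI.

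The section Surgical site infection population defines a narrower set, which "contains all patients included in the intention-to-treat population who have reached the study end (visit 6").

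The section Sensitivity analysis of the primary endpoint measure first repeats the primary analysis in the per-protocol and SSI populations. It then lists four further analyses, each assigned by name to the SSI population:
- (a) "in the surgical site infection population, all missing data will be imputed as surgical site infections in both groups";
- (b) the same, with missing data set to no SSI in both arms;
- (c) missing data set to SSI under NPIT and to no SSI under control;
- (d) "a time-to-event analysis will be performed in the surgical site infection population", by Kaplan–Meier.

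**The concern.** Analyses (a)–(c) are the usual extreme-case bounds for a binary endpoint. They are useful only where outcomes are missing, and here they are placed in a set defined by having reached the final visit. The patients whose outcomes the primary analysis must fill in, namely those who died or were lost before visit 6, have already been removed.

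The rule that a lost patient has no SSI is a strong single imputation. SSIs after discharge are a known problem, as the article's Discussion itself says. The protocol plans for about 10% drop-out (Sample size) or up to 15% (Sample size calculation), so the rule could apply to an appreciable share of patients. If the bounds are computed where there is almost nothing to bound, the report could show three agreeing sensitivity results although the dependence on the rule was never examined.

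This is not a detail left to an analysis plan. The protocol names the population for each analysis, and a plan that followed it would inherit the problem.

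**Working it through.** **1. Who can have a missing outcome in each set**

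| Patient | ITT | SSI population |
|---|---|---|
| Lost or withdrawn before visit 6 | in; no SSI if the outcome is missing | out |
| Died before visit 6 | in; SSI if the outcome is missing | out |
| SSI recorded at visits 3–5, then misses visit 6 | in | out |
| Reaches visit 6, wound not assessable (e.g. after relaparotomy) | in | in |

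Only the last row gives (a)–(c) anything to impute. With no such patient, all three equal the complete-case repeat in the SSI population. The per-protocol repeat also leaves out patients who miss visit 6 for reasons other than death or relaparotomy. No listed analysis therefore changes the imputed value of a lost patient.

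**2. Reproducing the planning figure**

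Inputs from Sample size calculation: the SSI rate "is approximately 25 % for the control group" and "can be reduced to 12.5 % in the experimental intervention arm"; chi-square test, 80% power, two-sided 5%.

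n per group = [1.960·√(2·0.1875·0.8125) + 0.842·√(0.25·0.75 + 0.125·0.875)]² / 0.125² = 151.9, rounded up to 152. This agrees with the section Sample size: "A total of 152 patients will be analyzed per group". With 10% drop-out, 152/0.90 = 168.9, in line with the 170 per group enrolled.

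**3. Illustration**

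Assumptions, not protocol figures: 170 randomised per arm; m lost in each arm, with no deaths or relaparotomies among them; SSI rates among the 170 − m observed as close to 12.5% v 25% as whole patients allow; every completer assessable. The test is the uncorrected chi-square for equal arms of size n, X² = (p₁ − p₂)² / [p̄(1 − p̄)·2/n].

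For m = 17 as written: 19/153 v 38/153, p̄ = 57/306 = 0.186, X² = 0.1242² / (0.186·0.814·2/153) = 7.78, p = 0.005.

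In the ITT population with m = 17 (NPIT v control):
- (a) (19+17)/170 v (38+17)/170 = 21.2% v 32.4%, p = 0.020
- (b) 19/170 v 38/170 = 11.2% v 22.4%, p = 0.006
- (c) (19+17)/170 v 38/170 = 21.2% v 22.4%, p = 0.79

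Over a range of losses:

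| Lost per arm | As written, (a)=(b)=(c) | (a) in ITT | (b) in ITT | (c) in ITT |
|---|---|---|---|---|
| 5 (3%) | 21/165 v 41/165, p = 0.005 | 26 v 46, p = 0.008 | 21 v 41, p = 0.005 | 26 v 41, p = 0.04 |
| 9 (5%) | 20/161 v 40/161, p = 0.004 | 29 v 49, p = 0.010 | 20 v 40, p = 0.004 | 29 v 40, p = 0.14 |
| 17 (10%) | 19/153 v 38/153, p = 0.005 | 36 v 55, p = 0.020 | 19 v 38, p = 0.006 | 36 v 38, p = 0.79 |
| 26 (15%) | 18/144 v 36/144, p = 0.007 | 44 v 62, p = 0.035 | 18 v 36, p = 0.008 | 44 v 36, p = 0.31 |

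ITT denominators are 170 per arm.

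**4. Kaplan–Meier**

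If every patient in the set is followed to day 30, nobody is censored earlier, and the day-30 estimate equals the crude proportion. The curve still shows when SSIs occur. It omits SSIs recorded in patients who later missed visit 6.

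**The case against.** It can fairly be said that four stronger readings, which a reader might infer, go too far.

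- **The set has no missing outcomes at all.** The definition asks for reaching visit 6, not for an assessable wound. The protocol names relaparotomy as a cause of missing data, and such a patient may attend visit 6. A few values could be imputed, and then (a)–(c) would not be exactly identical.
- **The lost-means-no-SSI rule has no other check.** The per-protocol and SSI-population repeats both leave out lost patients, so both are checks on it. They are complete-case checks, however, and bound nothing.
- **The analyses must always confirm the primary result.** They need not, because ITT counts outcomes missing through death as SSI and the SSI population drops those patients. With 17 non-completers per arm, suppose 8 under NPIT and 2 under control died. ITT is then (19+8)/170 v (38+2)/170 = 27/170 v 40/170, p = 0.076, against p = 0.005 in completers.
- **The worst case reverses the conclusion.** At 10% loss, (c) still slightly favours NPIT (21.2% v 22.4%); only significance goes. The direction turns at the 15% loss shown.

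Two further points stand. The protocol does not present (d) as a missing-data analysis, and a description of timing has its own use. The subgroup section also uses this population ("Prespecified subgroup analysis will be performed in the surgical site infection population for the depth of surgical site infection"), but running secondary analyses in completers is a design choice, and calling depth a subgroup is a matter of labelling. Neither adds weight here.

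None of this gives (a)–(c) a purpose in the set to which they are assigned.

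**Conclusion.** The point holds for (a)–(c). Their assigned population excludes nearly all the patients whose outcomes they are meant to impute, so they essentially repeat the complete-case analysis, and the primary rule for lost patients is never varied by imputation in the ITT population.

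The size depends on the losses that occur. In the illustration, moving to ITT leaves (a) and (b) significant at every loss shown, while (c) runs from p = 0.04 with 5 lost per arm to p = 0.79 with 17, and to a difference against NPIT with 26. These figures assume equal losses, the planned rates among those observed, and an unadjusted test in place of the planned logistic regression with centre effects. They show what the present plan would not reveal, and do not predict the trial's result.

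The primary estimate, its test and the sample size are untouched. This is a should-fix point. For (d), the supported criticism is narrower: the set discards SSIs seen before loss and takes away the censoring that the method is built to handle.

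**What to change.** In Sensitivity analysis of the primary endpoint measure:
- Run (a), (b) and (c) in the ITT population. State that (b) then differs from the primary rule only for outcomes missing through death or relaparotomy, so (a) and (c) carry the new information.
- Keep the SSI population for the complete-case repeat of the primary analysis.
- Run (d) in the ITT population so that SSIs recorded before loss are kept. Censor SSI-free patients at their last wound assessment, and handle death in line with the ITT rule. Treating death as a competing event instead would depart from that rule and would call for a cumulative-incidence method in place of Kaplan–Meier, so it would have to be stated and justified.

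The cost is a wording change and a few more analysis runs on data already scheduled for collection. It should be made before unblinding, because the same change made afterwards would look post hoc.

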#### Analysis populations

##### Intention-to-treat population

The intention-to-treat population contains all patients who have participated in visit 2 (surgery), independent of the intervention they receive (control or NPIT). Analysis will occur as randomized. Patients who unexpectedly receive a laparoscopic or laparoscopic assisted operation (exclusion criterion) will be excluded from the intention-to-treat population. Missing primary endpoint data in the intention-to-treat population will be treated as follows: data missing because of death or relaparotomy will be counted as surgical site infection in both groups. Data missing for other reasons (e.g., lost to follow-up) will not be counted as surgical site infection in either group.

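### Sensitivity analysis (c), the only missing-data scenario that differs by arm, is nearly empty as written and says little at the planned loss if applied to all randomised patients; a tipping-point grid would do better

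*Protocol article*

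**What the plan says.** Under Sensitivity analysis of the primary endpoint measure, the protocol article first repeats the primary analysis in the per-protocol and surgical site infection (SSI) populations. It then lists further analyses, all placed in the SSI population:

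- (a) missing counted as SSI in both arms;
- (b) missing counted as no SSI in both arms;
- (c) "missing data will be imputed as surgical site infections in the intervention group, but as non-surgical site infection in the control group";
- (d) a Kaplan–Meier analysis.

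The section on the SSI population limits that set to intention-to-treat patients who reached visit 6.

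For the primary analysis, the section Intention-to-treat population counts data missing through death or relaparotomy as SSI. For the rest it says: "Data missing for other reasons (e.g., lost to follow-up) will not be counted as surgical site infection in either group".

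Expected loss is given twice. Sample size has "Given an estimated drop-out rate of approximately 10 %, 340 patients will be randomized to the two treatment arms"; Sample size calculation has "Under the assumption of a drop-out rate of up to 15 %, a total of 340 patients (170 per group) need to be enrolled". The planned effect is a rate of "approximately 25 % for the control group" that "can be reduced to 12.5 % in the experimental intervention arm".

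**The concern.** The primary rule scores patients lost to follow-up as uninfected, so the reader needs to know how different the lost patients would have to be before the conclusion changes. Scenarios (a) and (b) treat the arms alike. For patients lost to follow-up, (b) also repeats the primary assumption; it departs from it only for data missing through death or relaparotomy. Only (c) lets the arms differ, and it does so at a single point: 100% infected among missing NPIT patients and 0% among missing controls.

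That rule adds to the NPIT arm nearly as many percentage points of infection as there are points of missing data, and it adds none to control. The planned loss is 10–15% and the whole planned effect is 12.5 points, so the two are of the same size. The report could then contain a prespecified analysis showing no benefit, or a higher rate under NPIT, although NPIT works as hypothesised and the loss is random. Nothing in the list would tell the reader how far from plausible that scenario is.

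**Working it through.** **Inputs from the article.** Control 25%, NPIT 12.5%, two-sided 5%, 80% power, 152 analysed and 170 randomised per group, drop-out about 10% or up to 15%.

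**The plan's own figure.** The two-proportion formula with pooled variance and no continuity correction gives 152 per group and 80.0% power, so the stated sample size reproduces. For the inflation, 152/0.90 = 169 per group (338 in total), which fits 340; 152/0.85 = 179 per group (358), which does not. The two drop-out figures disagree with each other. That is a separate matter, and both are used here as a range.

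**Literal reading of (c).** The SSI population holds visit-6 completers. Patients lost before visit 6 are outside it, so (c) has almost nothing to impute and roughly equals a complete-case analysis.

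**Reading of (c) in all randomised patients.** Assumptions: 170 per group; a fraction m missing in each arm, unrelated to infection; every drop-out is a missing endpoint with no SSI seen beforehand; unadjusted chi-square test in place of the planned logistic regression.

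- NPIT rate under (c) = 0.125(1 − m) + m
- Control rate under (c) = 0.25(1 − m)
- Remaining benefit = 0.125 − 1.125m, which is zero at m = 0.125/1.125 = 11.1%

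| Missing | NPIT | Control | Benefit left (points) | p at expected counts | Chance (c) significantly supports NPIT |
|---|---|---|---|---|---|
| 3% | 15.1% | 24.25% | 9.1 | 0.034 | 57% |
| 5% | 16.9% | 23.75% | 6.9 | 0.115 | 35% |
| 10% | 21.25% | 22.5% | 1.25 | 0.78 | about 5% |
| 15% | 25.6% | 21.25% | −4.4 | 0.34 | 0.2% |

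The last column is from simulation with binomial loss and outcomes. In the same simulation the estimate under (c) favours control in 37% of trials at 10% loss and in 81% at 15%, although the effect is fully real.

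If NPIT has no effect (25% in both arms), (c) shows significant harm in 54% of trials at 10% loss and in 87% at 15%.

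**What a tipping point would show.** Keep lost controls at 25% and let lost NPIT patients have risk q. The NPIT rate is 0.125(1 − m) + qm against 0.25, with 170 per group. Significance is lost (z below 1.96) once the NPIT rate reaches about 16.4%.

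- m = 0.10: q = (0.1639 − 0.1125)/0.10 ≈ 51%, about 4.1 times the observed 12.5%.
- m = 0.15: q = (0.1639 − 0.10625)/0.15 ≈ 38%, about 3.1 times.

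A reader can judge whether lost NPIT patients could plausibly be infected three or four times as often as the observed ones. The 100%/0% corner does not support that judgement.

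**The case against.** The strongest reply is that worst-case imputation is a standard bound, and a reasonable one when the primary rule scores lost patients as uninfected. The article sets no decision rule on (c) and nowhere requires it to be significant. This stands: (c) is not an error, and it should be kept.

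A reader might infer that the result of (c) is known in advance and that it wipes out the effect. The documents do not support that.

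- The outcome depends on actual missingness: support is 57% at 3% loss.
- It depends on the true effect. With the rates of the small colorectal trial cited under Previous trials (11/25 v 2/25), (c) would keep about 99.7% power at 10% loss and 89% at 15%.
- At 10% loss, 1.25 points of benefit remain.

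Planned drop-out is also not the missing-endpoint rate. Data missing through death or relaparotomy count as SSI, unexpected laparoscopic cases leave the intention-to-treat set, and wounds are assessed at several visits before day 30. Control infections seen before loss would count as observed, which makes (c) less extreme than calculated. The article does not give the share truly missing.

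A reader might also infer that the plan jumps from the primary assumption straight to extremes. It does not: the completer and per-protocol repeats cover the case where lost patients resemble observed ones.

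Finally, grid details are often left to an analysis plan that is not shown. That is fair, so the absence of a grid is not itself the fault. The point concerns what the article does fix: the population and the rule for (c).

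**Conclusion.** The point holds as a cheap improvement. On either reading (c) contributes little at the planned loss. Taken literally, it is nearly empty. Applied to all randomised patients, it leaves 1.25 of 12.5 points at 10% missing and reverses to −4.4 points at 15%, with about a 5% and a 0.2% chance of supporting a fully real effect. A failed (c) at that loss could not separate a fragile result from a sound one. Passing it, which is realistic if few endpoints are missing or the effect is larger than planned, would be strong evidence of robustness.

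These figures assume equal random loss in both arms, all drop-out as missing endpoints, the hypothesised rates among observed patients and an unadjusted test. With fewer missing endpoints the problem shrinks, as the 3% and 5% rows show.

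**What to change.** 1. Run the missing-data scenarios (a) to (c) in the intention-to-treat set, where the patients with missing outcomes are, and bring the definition of the SSI population into line with this.
2. Keep (a) and (c), labelled as bounds and not as checks the result is expected to pass.
3. Add a tipping-point analysis. Vary the SSI risk of patients with missing outcomes from 0% to 100% separately in each arm, with the observed arm rate as the reference point, and repeat the primary analysis at each grid point. Report the risk among lost NPIT patients at which the primary conclusion changes. Scenarios (a) and (c) are corners of this grid.

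The cost is a sentence or two in the analysis section and a short program loop, with no new data or patients. The downside is a grid or plot that needs interpretation where the present text gives a single p-value.

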#### Prespecified subgroup analysis

Prespecified subgroup analysis will be performed in the surgical site infection population for the depth of surgical site infection (superficial versus deep versus organ space; Table 1) in both groups (NPIT versus control). Furthermore, the rate of all surgical site infections will be analyzed in the surgical site infection population in the following subgroups: (a) National Nosocomial Infection Surveillance risk score (0 versus 1 versus >1); (b) body mass index (<25 versus >25); (c) grade of contamination (clean versus clean-contaminated versus contaminated versus dirty, as defined by the CDC, [9]); (d) American Society of Anesthesiology score (1 and 2 versus 3 versus ≥4); (e) presence of an ostomy (yes versus no); (f) skin preparation used (ethanol-based versus isopropyl-alcohol-based versus chlorhexidine-based versus Povidone-iodine-based); (g) age (≤65 versus > 65 years), (g) cause of surgery (malignant versus benign surgery).

#### Analysis of secondary endpoint measures

All secondary endpoints will be analyzed using descriptive statistical methods and comparisons between groups will be performed with the appropriate statistical tests. For comparisons of frequencies between groups, the chi-square test and, if appropriate, the Fisher exact test, will be used. As appropriate, Student’s *t* test, the Mann–Whitney U test or analysis of covariance (ANCOVA) will be employed for group comparisons of quantitative data. All tests will be two-sided at a significance level of 5 %.

#### Safety analysis

For safety analysis, all adverse and serious adverse events will be analyzed via descriptive statistical methods. For comparisons of frequencies between groups, the chi-square test and, if appropriate, the Fisher exact test, will be used. Patients who have started visit 2 (operation) will be analyzed as treated.

Procedures for the statistical analysis of the primary and secondary endpoint measures will be conducted in line with the GCP-ICH E9 guideline [40]. For the statistical analysis, IBM SPSS Statistics version 21.0 will be used (IBM Corp., Armonk, NY). Statistical analysis will be performed by a group-allocation blinded statistician from the Institute for Medical Statistics and Epidemiology of the Technische Universität München.

